### **Procedures**

Once the patient has given consent they will be randomised by the Trial Manager at King's ([name]). The Trial Manager will inform the patient about the outcome of this randomisation and when they can expect to hear from the MPCT. The Trial Manager will contact you as the MPCT once a patient is supposed to receive the SIPC intervention, with the details of the patient. Patients should not be able to receive SIPC unless they have been referred through the study. We have completed mapping which shows that patients with LTNCs don't usually receive specialist palliative care, so we are not denying patients anything that they currently receive.

**You are encouraged to have no direct contact with the patient until these details have been received nor to take referrals for the trial from any other source.**

The patients will be assigned to receive either Short Term Integrated Palliative Care (SIPC) or Standard Care.

### **Short Term Integrated Palliative Care (SIPC)**

This group of patients will be offered the short term integrated palliative care service delivered by a MPCT straight away.

### **Standard Care**

This is the control group and for the next twelve weeks this group of patients will continue with their usual care from their neurologist, specialist nurse and community teams. At the end of the twelve week period you will be notified the details of these patients and they will be offered the short term integrated palliative care intervention. You should not offer specialist palliative care to this group before this time, and their details will not have been sent to you by the Trial Manager.

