### **14.4 Subject Compliance & Adherence**

We will record and classify the level of adherence (compliance) in both intervention and control arms. This will be kept under review by the trial co-ordinator (as the research nurses will be blinded to the intervention). We estimate that we will classify compliance as follows (using a standard nomenclature), based on a combination of the research (patient interviews about particular services received, trial co-ordinator log, research nurse log) and clinical records (log kept by clinicians), and contact with clinical services:

- Complier (receives full intervention as planned)
- Partial complier / erratic user (receives some of intervention but not all, or recommendations not followed)
- Overuser (in frequent contact with the service)
- Contamination (when the control group access the service before due – cause will be recorded)
- Dropout –cause recorded using the MORECARE classification of reason for attrition [44]

Definitions of compliance and ways to assess these will be refined during the intervention development and mapping phase of the project. We will also monitor and review the recruitment rate and the adherence to the protocol and respond appropriately if necessary.

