### 18.2 Secondary Efficacy Parameters

- 1) Patients' palliative needs and symptoms: Integrated Palliative care Outcome Scale for neurological conditions (IPOS Neuro) (based on a commonly used and well validated measure in palliative care research and clinical practice) [4 67-70];
- 2) Patients' health-related quality of life and well-being: EQ-5D and ICEpop CAPability measure for Adults (ICECAP-A) [71]. EQ-5D is a 5 item measure (mobility, self-care, usual activities, pain/discomfort, anxiety/depression) used to generate quality adjusted life years (QALYs). It has been used in numerous economic evaluations including those for neurological conditions. It will be the main measure in the cost-effectiveness analysis. The ICECAP-A is a new capability/well-being measure for use in economic evaluations. It has 5 items (feeling settled and secure; love, friendship and support; being independent; achievement and progress; enjoyment and pleasure) each scored 1-4 [72]. The possible states derived from the ICECAP-A are currently being valued in a way appropriate for QALY calculations (this will be completed before our analyses). QALYs generated will be used in secondary cost-effectiveness analyses; or the Integrated Palliative Outcome Scale for neurological conditions (IPOS Neuro);

- 3) Patients' psychological distress: Hospital Anxiety and Depression Scale (HADS) (patient reported);
- 4) Patients' satisfaction, self-efficacy and other aspects: patient satisfaction scale (modified FAMCARE-P16) [73], Self-Efficacy to Manage Chronic Disease Scale (SEMCD), an advance care planning scale (as used by Tuck et al 2013 [74]) and some questions covering patients' experiences of the study;
- 5) Hospital, service use and survival: hospital admissions, length of hospital stay and emergency attendances during the study and other health service use extracted from clinical records and also recorded using an adapted version of the Client Service Receipt Inventory (CSRI) at 0, 12, and 24 weeks [75]. The CSRI has been used in around 300 studies internationally. Services will include specialist palliative care, other primary and secondary healthcare, medication, social care, and care from family members. Where possible we will supplement CSRI data with data from hospital-based information systems. Employment status and welfare benefits will also be recorded. Survival (days from consent to death) for those patients who die irrespective of cause, will also be evaluated;

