This manual complements the trial protocol document which is the definitive trial document. Please refer to the protocol document for further details related to trial procedure.

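### The intervention manual tells local teams not to offer specialist palliative care to controls before week 12, with no exception for urgent or end-of-life need, and the protocol states no exception either

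*Protocol*

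**What the plan says.** The manual's Section 2, under Standard Care, sets a twelve-week period of usual care for controls and instructs the delivering team: "You should not offer specialist palliative care to this group before this time, and their details will not have been sent to you". Under Procedures, the same section adds: "You are encouraged to have no direct contact with the patient until these details have been received". It justifies the wait by saying that these patients do not usually receive specialist palliative care, "so we are not denying patients anything that they currently receive". The teams addressed are existing clinical services (protocol Sections 8 and 14.1), not units created for the trial.

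The manual ranks itself below the protocol: "This manual complements the trial protocol document which is the definitive trial document".

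The protocol treats early access differently. Section 14.4 has a contamination class, "when the control group access the service before due", with the cause to be recorded. Section 18.2 collects service use through the CSRI: "Services will include specialist palliative care, other primary and secondary healthcare". Sections 19.3 and 20.2.1 set a limit of 10% of controls receiving specialist palliative care within 11 weeks of randomisation, once as a stopping rule and once as a criterion for continuing.

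**The concern.** The population has advanced, progressive disease, and some controls can be expected to deteriorate or approach death during the wait. Section 20.1 allows 20% attrition to week 12 and cites 3 of 52 lost to death or illness in the phase II trial.

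The manual provides for need-based continuing palliative care, including for patients close to dying (Section 3; Standard Operating Procedures, item 16), but only for patients already receiving SIPC. Nothing parallel is written for waiting controls. A clinician who follows the Standard Care instruction to the letter could hold back care from a control whose neurologist or GP has referred them urgently. What is at stake is the care of that patient and the trial's position if it happens, not the validity of the week-12 comparison.

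**Working it through.** The point turns on wording, so the first step is to compare the texts.

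1. **Scope of the manual's rule.** It names specialist palliative care, which is wider than SIPC. No exception for urgent need, deterioration or dying appears there or elsewhere in the manual.
2. **What the protocol adds or removes.** It contains no such prohibition. A limit above zero and a field for cause presuppose that a few controls will receive this care. But the protocol calls early access contamination, caps it, and sets the same wait of about 12 weeks (Sections 8 and 14.1, Figure 3). It nowhere says that such care may be given on clinical need.
3. **Other routes in the protocol.** Section 17.3 directs severe distress to the patient's healthcare team or the neurology team. Section 16.5 protects usual care on withdrawal. Section 19.1 monitors deaths and admissions. None names an urgent palliative route for a control.
4. **When the rule could bite.** Controls' details are not sent to the teams, so a team must learn the allocation in another way. It can, because "The Trial Manager will inform the patient about the outcome of this randomisation", and the patient or family may pass it on.

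The arithmetic concerns only the room available for an exception.

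*The 10% limit.* With 178 controls (Section 9), 0.10 × 178 = 17.8. Then 17/178 = 9.55%, within the limit, and 18/178 = 10.11%, over it.

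*At the formal review.* The minimum recruitment is 25 patients (Section 20.2.1). Assuming near-equal 1:1 allocation, 12 or 13 are controls. One case is 1/13 = 7.7% or 1/12 = 8.3%. Two cases are 2/13 = 15.4% or 2/12 = 16.7%, which is over the limit.

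*Cost in power.* The plan's own figure first. With effect 0.30, correlation 0.40, two-sided alpha 0.05 and 80% power (Section 20.1), n per arm = 2 × (1.960 + 0.842)² × (1 − 0.40²) / 0.30² = 2 × 7.85 × 0.84 / 0.09 = 146.5, so 147 against the stated 148. Power at 148 per arm is 80.4%. If a fraction c of controls received the care and gained its full effect, the difference would shrink to 0.30 × (1 − c):

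- c = 2%: difference 0.294, power 78.8%
- c = 5%: difference 0.285, power 76.3%
- c = 10%: difference 0.270, power 71.7%

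The full-effect assumption is mine. The values of c illustrate a range and do not forecast how often the exception would be used.

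**The case against.** The strongest reply is that the manual only tells teams to keep to the comparator that the protocol defines. To offer is to start a service; it is not the opposite of declining a referral. The same sentence says that the team will not hold the controls' details, which fits a bar on initiating care. The Procedures text only encourages teams to avoid contact, and its bar on other referrals is confined to referrals for the trial. Sites also have hospices, community services and hospital support teams (Section 15). Usual care continues in both arms (Section 14.1), and patients may withdraw at any time (Section 16.5). The consent pages are not available, so what controls were told about access to care cannot be seen. All of this stands, and it narrows the practical reach.

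A reader might infer that the manual contradicts a protocol that permits early palliative care on need. The documents do not support this: a cap on contamination is not permission, and the protocol is silent on clinical need. A reader might also infer that dying controls must be refused, or are cut off from palliative care altogether. The text does not say so, and it addresses only the teams delivering the intervention. Nor is the reassurance about not denying care false as written, because patients with current or recent specialist palliative care are excluded (Section 16.2).

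The reply does not supply a written exception. Whether a team accepts an urgent referral of a known control is left to how one clinician reads one sentence, and the definitive document does not settle it.

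**Conclusion.** The point holds in a limited form. The manual states an unqualified rule covering all specialist palliative care, and neither it nor the protocol says what happens when a control has urgent or end-of-life need before week 12. The rule matters only if three things coincide: usual clinicians refer the patient to a trial team, that team knows the allocation, and it reads the instruction as a reason to decline. The documents give no figure for how often this would occur, and none is estimated. No bias in the week-12 estimate is claimed. This is a cheap improvement on grounds of patient safety, not a defect in the analysis.

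**What to change.** Keep the bar on initiating palliative care for controls. Do not narrow the rule to SIPC: the manual describes SIPC as only a slight variation on specialist palliative care, so the same teams could then give nearly the same care early.

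Add one sentence to the manual's Standard Care text and to the control-arm paragraph of protocol Section 14.1, for example: *A control patient referred by their usual clinicians for end-of-life care, or for an acute deterioration that the referring clinician judges cannot wait until week 12, is accepted as in routine practice; the referral is notified to the Trial Manager, recorded as contamination with its cause, and the patient stays in the intention-to-treat analysis.*

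The exception should be tied to dying or acute deterioration because every eligible patient already has an unresolved symptom (Section 16.1), so a general need clause would admit almost anyone. Notification must bypass the blinded research nurses. Section 14.4 already gives the oversight of adherence to someone else: "This will be kept under review by the trial co-ordinator (as the research nurses will be blinded to the intervention". Because the contamination class there refers to the service, the new sentence should make clear that it also covers specialist palliative care given by the trial team outside SIPC.

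Sample size, visits and the analysis do not change. The cost is slightly more contamination, counted against the 10% limit. Two such patients among 12 or 13 controls would exceed that limit at the formal review, so the count should go to the SSC and DMEC together with the causes.

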### **3. Timelines for the intervention and outline of response after referral and visits**

The length of intervention is usually 6-8 weeks from referral. Specialist palliative care is always an individualised service, responding to patients needs and SIPC is intended to be the same. Therefore, there should be some flexibility to adjust to patient and families individual needs and requirements, and some patients will need quicker support after the first or second visit. Each visit is expected to last 60-90 minutes. A small number (based on previous experience, 10%) will need continuing palliative care support and this will be provided on a needs basis. It is anticipated that the teams will have usually put in place the systems for improved care and have resolved immediate issues. The majority of patients and caregivers will be able to be discharged with no formal follow up after the third visit. A small number of patients and caregivers may also need only 2 visits and phone contact.

**First telephone contact (made within 2 working days of referral, sooner if urgent, if longer than this time reasons recorded).**

Date contact made and the time it takes for this telephone contact to be recorded on the clinical contact form (Appendix 2). Initial introductions, explain role of team, review of symptoms and concerns of patient and if appropriate family, limited telephone palliative care assessment. Agree date and time for first visit. Location can be at patients home or in other location (e.g. hospital if patients is attending outpatients or elsewhere) as mutually agreed. Consultation with colleagues in palliative care team and contact with any other relevant professionals (e.g. neurology, primary care, rehabilitation) as required for background information

#### **Visit 1**

**Visit from key worker, a specialist in palliative care (nurse, doctor or other) within 5 working days from first telephone contact. Record the time taken for the visit including travel on the usual clinical record form.**

Comprehensive palliative care assessment (for more detail see section 4) recorded on the usual clinical record form covering:

- Completion of IPOS Neuro
- Symptom control and management
- Continuity and co-ordination of care, access to services
- Psychosocial needs
- Information / communication needs
- Advance care planning
- Assessment of caregiver
- Generate an agreed personalised problem list and action plan including agreement of plan for next visit/contact
- Patient/family given information about the SIPC and what is provided and given contact details
- Patient is discussed in Multi-disciplinary team meeting using the MDT proforma (Appendix 3). When this is completed, this is then sent to the patient and all relevant health professionals.

### **After 1st visit**

Review problem list/plan from first visit with multi-professional team & liaise with relevant health, social and voluntary sector professions to ensure other services are provided or other needs met.

- Contact with patient/ family as agreed in plan and as required. All contacts made with the patient/carer or with health professionals outside the study visits need to be documented in the clinical contact form (Appendix 2).
- Contact to confirm second visit.

### **Visit 2**

**This will usually be within two weeks of visit 1**

**Visit from key worker or other relevant team member- Record the time taken for the visit including travel on the usual clinical record form.**

Review outcomes from actions already taken.

Reassessment covering areas as for visit 1.

If immediate issues have resolved, explore needs and wishes for advance care planning. Revise personalised plan and actions.

Discuss plan for discharge.

### **After 2nd visit**

- Liaise with relevant health professionals and provide information, education, advice and co-ordination to health professions as required. Re-review personalised problem list/plan with multi-professional team and complete MDT proforma. When this is completed, this is then sent to the patient and all relevant health professionals.
- Contact with patient/ family as agreed in plan and as required. All contacts made with the patient/carer or with health professionals in relation to the patient outside the study visits need to be documented on the clinical contact form (Appendix 2).
- Contact to confirm third visit

### **Visit 3**

**This will usually be 3-4 weeks after visit 2**

**Visit from key worker or other relevant team member- Record the time taken for the visit including travel on the usual clinical record form.**

Review outcomes from actions already taken

Reassessment, revise plan

Reassessment repeated as required

### **Discharge**

- Final Review with multi-professional team & liaison with relevant health professions to ensure services in place. Re-review personalised problem list/plan with multi-professional team and complete MDT proforma. When this is completed, this is then sent to the patient and all relevant health professionals.

#### **4. Topics to be covered in the Assessment**

We would like you to use the IPOS Neuro staff questionnaire shown below to ascertain the problems that the patient identifies as important to them.

The research nurses will be using the patient version of IPOS Neuro during the research visits this differs very slightly from the staff version.

**We are asking the clinical teams to use the staff version (as described in the protocol) as a way of making sure everything is covered during the clinical review**

Patient name: .....  
 Patient DOB: .....  
 Date completed: .....

[figure not shown]

www.pos-pal.org

## IPOS Neuro Staff Version

**Q1. What have been the patient's main problems or concerns over the past 3 days?**

- 1.....
- 2.....
3. ....

**Q2. Please tick one box that best describes how the patient has been affected by each of the following symptoms over the past 3 days?**

|                                                   | Not at all                 | Slightly                   | Moderately                 | Severely                   | Over-
whelmingly        | Cannot
assess (e.g.
unconscious) |
|---------------------------------------------------|----------------------------|----------------------------|----------------------------|----------------------------|----------------------------|----------------------------------------|
| Pain                                              | 0  | 1  | 2  | 3  | 4  |                |
| Shortness of breath                               | 0  | 1  | 2  | 3  | 4  |                |
| Nausea (feeling like you
are going to be sick) | 0  | 1  | 2  | 3  | 4  |                |
| Vomiting (being sick)                             | 0  | 1  | 2  | 3  | 4  |                |
| Poor appetite                                     | 0  | 1  | 2  | 3  | 4  |                |
| Constipation                                      | 0  | 1  | 2  | 3  | 4  |                |
| Sore or dry mouth                                 | 0  | 1  | 2  | 3  | 4  |                |
| Drowsiness                                        | 0  | 1  | 2  | 3  | 4  |                |
| Poor mobility                                     | 0  | 1  | 2  | 3  | 4  |                |
| Spasms                                            | 0  | 1  | 2  | 3  | 4  |                |

|                                                           | Not at all                 | Slightly                   | Moderately                 | Severely                   | Over-
whelmingly        | Cannot
assess (e.g.
unconscious) |
|-----------------------------------------------------------|----------------------------|----------------------------|----------------------------|----------------------------|----------------------------|----------------------------------------|
| Fatigue or lack of energy                                 | 0  | 1  | 2  | 3  | 4  |                |
| Problems swallowing                                       | 0  | 1  | 2  | 3  | 4  |                |
| Feeling sleepy                                            | 0  | 1  | 2  | 3  | 4  |                |
| Difficulty in sleeping                                    | 0  | 1  | 2  | 3  | 4  |                |
| Difficulty with bowel control                             | 0  | 1  | 2  | 3  | 4  |                |
| Difficulty controlling urine                              | 0  | 1  | 2  | 3  | 4  |                |
| Pressure Sores                                            | 0  | 1  | 2  | 3  | 4  |                |
| Problems using your arms                                  | 0  | 1  | 2  | 3  | 4  |                |
| Problems using your legs                                  | 0  | 1  | 2  | 3  | 4  |                |
| Difficulty communicating                                  | 0  | 1  | 2  | 3  | 4  |                |
| Dribbling of Saliva                                       | 0  | 1  | 2  | 3  | 4  |                |
| Falls                                                     | 0  | 1  | 2  | 3  | 4  |                |
| Hallucinations                                            | 0  | 1  | 2  | 3  | 4  |                |
| Mouth Problems                                            | 0  | 1  | 2  | 3  | 4  |                |
| Loss or change in your ability to taste or smell          | 0  | 1  | 2  | 3  | 4  |                |
| Unexplained change in weight (not due to change in diet). | 0  | 1  | 2  | 3  | 4  |                |

|                                                                                     | Not at all                 | Slightly                   | Moderately                 | Severely                   | Over-
whelmingly        | Cannot
assess (e.g.
unconscious) |
|-------------------------------------------------------------------------------------|----------------------------|----------------------------|----------------------------|----------------------------|----------------------------|----------------------------------------|
| Problems remembering things that have happened recently or forgetting to do things. | 0  | 1  | 2  | 3  | 4  |                |
| Loss of interest in what is happening around you or in doing things.                | 0  | 1  | 2  | 3  | 4  |                |
| Difficulty concentrating or staying focused.                                        | 0  | 1  | 2  | 3  | 4  |                |
| Feeling less interested in sex or more interested in sex.                           | 0  | 1  | 2  | 3  | 4  |                |
| Finding it difficult to have sex when you try.                                      | 0  | 1  | 2  | 3  | 4  |                |
| Feeling light-headed, dizzy or weak standing from sitting or lying.                 | 0  | 1  | 2  | 3  | 4  |                |
| Excessive sweating                                                                  | 0  | 1  | 2  | 3  | 4  |                |
| Double vision                                                                       | 0  | 1  | 2  | 3  | 4  |                |

Please list any other symptoms and tick one box to show how you feel each of these symptoms has affected the patient over the past 3 days.

|    |                            |                            |                            |                            |                            |                          |
|----|----------------------------|----------------------------|----------------------------|----------------------------|----------------------------|--------------------------|
| 1. | 0  | 1  | 2  | 3  | 4  |  |
| 2. | 0  | 1  | 2  | 3  | 4  |  |
| 3. | 0  | 1  | 2  | 3  | 4  |  |

